### Sample size calculation

In our prospective study conducted from January 2023 to June 2023, we enrolled 50 eligible patients undergoing same-visit bidirectional endoscopy under propofol-based sedation. The results indicated that 8 patients (16%) experienced desaturation and 7 patients (14%) developed hypotension (unpublished data). These incidences are consistent with the recent literature [22]. Prior studies have demonstrated that the addition of lidocaine to propofol for painless gastroenteroscopy or retrograde cholangiopancreatography can reduce the incidence of respiratory depression and hypotension by approximately 8 to 30% [12,13]. Based on these findings, we hypothesize that the addition of lidocaine will reduce the incidence of respiratory depression and hypotension by 10%, lowering their combined occurrence to 20%. Assuming a two-sided significance level (α) of 0.05 and a power (1-β) of 80%, a total of 290 patients per group will be required. Accounting for an anticipated dropout rate of 10%, we plan to recruit a total of 648 patients, with 324 allocated to each group. Sample size calculations were performed using the PASS software (Version 15, PASS Institute Inc.).

### Statistical analysis

Continuous variables will be assessed for normality using the Shapiro–Wilk test and will be presented as mean ± standard deviation (SD) for normally distributed data, or as median with interquartile range (IQR) for non-normally distributed data. Between-group comparisons will be conducted using the independent-samples t-test or the Mann–Whitney U test, depending on the distribution. Categorical variables will be reported as counts (percentages) and compared using the chi-squared test or Fisher’s exact test, as applicable.

Demographic and baseline characteristics will be summarized using descriptive statistics and standardized mean differences will be reported to assess the balance between groups. For study outcomes, the treatment effects between the two groups will be evaluated using odds ratios (OR) or mean differences (MD), each accompanied by 95% confidence intervals (CI). Additionally, outcomes will be further analyzed using multivariate logistic regression or generalized linear models, adjusting for relevant baseline covariates (age, BMI, history of hypertension, chronic obstructive pulmonary disease [COPD], and diabetes mellitus) and study center. Subgroup analyses of the primary outcome will be conducted to explore potential differential effects of the intervention across predefined subgroups, including BMI (< 25 kg/m^2^ vs ≥ 25 kg/m^2^), history of hypertension (yes vs no), history of COPD (yes vs no), history of diabetes mellitus (yes vs no), and study center (leading center vs participating center), with interaction effects evaluated using logistic regression. Sensitivity analyses will evaluate individual components of the primary outcome and the sedation-related adverse events (desaturation, hypotension, dizziness, headache, nausea and vomiting). Correction for multiple comparisons among secondary outcomes will be performed using the Benjamini–Hochberg method to control the false discovery rate.

All analyses will follow the modified intention-to-treat principle, including all randomized patients who undergo same-visit bidirectional endoscopy under sedation and have available primary outcome data. Protocol deviations are expected to be minimal. No interim analyses or imputation for missing data are planned. All statistical tests will be two-sided, with a P value < 0.05 considered statistically significant. Statistical analyses will be performed using R software (version 4.3.0; R Foundation for Statistical Computing).

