### Randomization and blinding

An independent statistician, who is not involved in the study, will generate the randomization list using an online tool (https://www.sealedenvelope.com/simple-randomiser/v1/lists). Participants will be randomized in a 1:1 ratio using permuted block sizes of 2 and 4, stratified by study center. The randomization assignments will be prepared and sealed in sequentially numbered, opaque envelopes by an independent research assistant who is not engaged in participant recruitment, intervention administration, or outcome assessment. These envelopes will be securely stored until allocation. An independent researcher, responsible for patient enrollment, will open the corresponding envelope to obtain the randomization assignment and prepare the sedation medications accordingly. All patients will receive either lidocaine or normal saline according to the randomization schedule. As both lidocaine and normal saline are clear and colorless solutions, the contents of the syringes will be visually indistinguishable. To minimize the risk of unblinding associated with lidocaine administration, a low dose of sufentanil will be administered at the initiation of anesthesia induction, and intravenous access will be established *via* the antecubital vein [15]. Patients, peri-procedure anesthesiologists, gastroenterologists, and outcome assessors remain blinded to the assigned treatment groups.

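### The centre-adjusted model is better suited than the unadjusted chi-squared test to be the primary analysis, and a risk difference should stand beside the odds ratio (free improvement)

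*Protocol article*

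**What the plan says.** Under Randomization and blinding, allocation is 1:1 in permuted blocks, "stratified by study center"; there are four hospitals.

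Under Statistical analysis, the first method given for a binary outcome is unadjusted: "Categorical variables will be reported as counts (percentages) and compared using the chi-squared test" or Fisher's exact test. Effects are to be "evaluated using odds ratios (OR) or mean differences (MD"), with 95% confidence intervals. Then, as an addition, "outcomes will be further analyzed using multivariate logistic regression or generalized linear models, adjusting for relevant baseline covariates" (age, BMI, hypertension, COPD, diabetes) and study centre. P < 0.05 applies to every test. The multiplicity correction covers the secondary outcomes only. No risk difference or risk ratio is planned.

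The Discussion says that the covariate adjustment is meant to reduce bias and sharpen the estimate of the treatment effect.

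Under Sample size calculation, lidocaine is expected to "reduce the incidence of respiratory depression and hypotension by 10%, lowering their combined occurrence to 20" percent, and "Assuming a two-sided significance level (α) of 0.05 and a power (1-β) of 80%, a total of 290 patients per group will be required".

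Under Data collection, blood pressure and SpO2 are recorded at baseline. Neither is among the listed covariates.

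**The concern.** A factor used to stratify randomisation is normally carried into the primary analysis. If it is left out and event rates differ by centre, the unadjusted test treats between-centre variation as noise: its true error rate falls below 5% and power is lost. Here the analysis that keeps centre is already specified but comes second, while the Discussion describes it as the better estimator.

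Two further matters follow. Both analyses carry the 0.05 threshold, so a reader could meet two P values for the primary outcome that fall on different sides of it. The crude and adjusted odds ratios also target different quantities, because the odds ratio is not collapsible; they can differ with no imbalance between arms. Finally, the trial was sized on a difference in percentage points, and the planned effect measure does not state that difference.

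**Working it through.** **1. The plan's own figure.** Inputs from Sample size calculation: two-sided alpha 0.05, power 80%, lidocaine rate 20%, control rate 30%. The control rate is implied by 20% + 10 points and by 16% + 14% ("8 patients (16%) experienced desaturation and 7 patients (14%) developed hypotension"); it is not stated as a composite rate.

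- Unpooled formula: n = (1.960 + 0.842)² × (0.30×0.70 + 0.20×0.80) / 0.10² = 7.849 × 0.37 / 0.01 = 290.4.
- Pooled formula: n = [1.960×√(2×0.25×0.75) + 0.842×√0.37]² / 0.10² = 294 after rounding up. Power at 290 per group on this formula is 79.6%.
- Dropout: 291/0.9 = 323.3, so 324 per group, as planned.
- A relative 10% reduction (30% to 27%) would need 3,554 per group. Only the absolute reading reproduces 290.

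So the trial is sized as an unadjusted comparison of two proportions on the absolute scale.

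**2. Effect scale.** At 30% versus 20%: RD = 10 points; RR = 0.20/0.30 = 0.67; OR = (0.20/0.80)/(0.30/0.70) = 0.583. With that OR held fixed, the lidocaine odds are 0.583 × p/(1−p), where p is the control rate:

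| Control rate | Lidocaine rate | Absolute reduction |
|---|---|---|
| 16% | 10.0% | 6.0 points |
| 28% | 18.5% | 9.5 points |
| 30% | 20.0% | 10.0 points |
| 40% | 28.0% | 12.0 points |
| 60% | 46.7% | 13.3 points |

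One OR therefore corresponds to different absolute effects. Sizing on the log OR instead gives n = 7.849 × (1/0.21 + 1/0.16) / 0.539² = 297.5, or 298 per group, so the choice of scale hardly moves the sample size.

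**3. Unadjusted against adjusted.** The documents give no centre-specific rates and no covariate effects, so these are assumed. Simulation: 584 analysed, four equal centres, conditional OR 0.583, 5,000 replicates under the null and 2,500 under the effect. Centre effects are evenly spaced on the logit scale with SD 0, 0.5 or 1.0. From logit(0.30) = −0.847, SD 0.5 gives outer centres at −0.847 ± 0.671, that is control rates of 18% and 46%. SD 1.0 gives −0.847 ± 1.342, that is 10% and 62%. Prognostic covariates means two continuous (log-OR 0.5 per SD) and three binary (log-OR 0.7, 0.7, 0.3).

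| Centre SD | Covariates prognostic | Type I error: unadjusted / adjusted / smaller P | Power: unadjusted / adjusted | Disagree on significance (under the effect) | Mean OR: unadjusted / adjusted |
|---|---|---|---|---|---|
| 0 | no | 5.4 / 5.4 / 5.8% | 81.5 / 81.5% | 2.4% | 0.58 / 0.58 |
| 0 | yes | 4.6 / 5.1 / 6.4% | 72.4 / 77.7% | 8.8% | 0.62 / 0.57 |
| 0.5 | no | 4.2 / 4.9 / 5.1% | 78.2 / 79.4% | 2.7% | 0.60 / 0.58 |
| 0.5 | yes | 4.3 / 4.6 / 6.0% | 70.2 / 76.9% | 11.1% | 0.63 / 0.57 |
| 1.0 | no | 2.7 / 5.1 / 5.2% | 71.8 / 77.3% | 5.6% | 0.63 / 0.58 |
| 1.0 | yes | 3.3 / 4.8 / 5.5% | 64.4 / 75.0% | 13.0% | 0.66 / 0.57 |

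Compare within rows only. A fixed conditional OR gives a smaller marginal effect as heterogeneity grows, so the fall down the unadjusted column is not all due to the omission of centre.

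**4. Other assumptions.** With 290 per arm and centre control rates of 25-35%, unadjusted and centre-adjusted power differed by at most 0.5 points, and the two tests disagreed in at most 0.6% of trials. With rates of 15-50% the gain from adjusting for centre was about 2-3 points. Adding one covariate of log-OR 0.5-0.8 per SD, a separate simulation gave 81% unadjusted, 83-84% with centre and 86-88% with centre and covariate. Always taking the smaller P gave 5.8-6.9% type I error there (5.5-6.7% in a repeat), but 4.6-6.0% with a weak covariate (log-OR 0-0.2).

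**The case against.** The strongest reply is that the plan already implies a ranking. The unadjusted comparison comes first, the model is introduced as an addition, and the sample size is that of an unadjusted comparison. The covariate list is fixed in advance. Data collection refers to a prespecified statistical analysis plan, which is not shown and may name the decisive analysis. This stands: the article does not set up two rival primary analyses, and the absence of an explicit label is not the point. What remains is that the implied order puts the weaker method first, and that the Discussion's praise of the adjusted model pulls against that order.

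Four stronger conclusions that a reader might draw are not supported:

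- *The unadjusted test is invalid or inflates error.* It does not; it is conservative when centres differ. Nor does the plan ignore centre, which is in the additional model.
- *The plan inflates type I error.* That happens only if someone picks the smaller P after seeing the results, and the size depends on assumed covariate strength.
- *The odds ratio is wrong.* It is a legitimate measure. The general hypothesis in the Introduction and Discussion is a lower incidence with no scale, and percentages by arm will be reported, so a reader can take the crude difference. What is lacking is a planned absolute estimate with an interval.
- *Omitting baseline SBP and SpO2 is an error.* Nothing in the documents shows how strongly they predict the composite, and related histories (hypertension, COPD) are already listed. Adding them is an improvement.

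**Conclusion.** This is a free improvement, not the correction of an invalid plan. The gain in power ranges from nothing (similar centres, weak covariates) through 2-3 points (control rates of 15-50% across centres) to about 10 points in the most extreme scenario simulated (64.4% against 75.0%). With about 80% power at 290 per group, the design has little to give away. Disagreement on significance in 2-13% of trials is a range over assumed scenarios under the planned effect. Error from choosing the smaller P is at most about 6-7% with strong covariates and near 5% with weak ones.

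What does not depend on those assumptions is that the stratification factor is missing from the comparison listed first, and that no planned estimate expresses the 10-point reduction used to size the trial.

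**What to change.** Before database lock and unblinding, state one primary analysis: logistic regression of the composite on treatment, study centre, age, BMI, hypertension, COPD, diabetes, baseline SBP and baseline SpO2, with the treatment term tested at two-sided 0.05.

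From that model report the standardised (marginal) risk difference with 95% CI beside the odds ratio. It is the average over all analysed patients of the predicted risk under lidocaine minus the predicted risk under saline. Keep the unadjusted chi-squared test as supportive.

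The cost is a few sentences. The variables are already recorded, and the plan to recruit 648 patients stands. Because no imputation is planned, the text should also say how a patient with a missing baseline value enters the model.

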## Discussion

This multicenter, randomized, double-blind, parallel-controlled trial will include 648 eligible patients to evaluate the effects of intravenous lidocaine versus normal saline placebo on the incidence of desaturation and hypotension during same-visit bidirectional endoscopy. Furthermore, we will assess the total propofol consumption, incidence of involuntary body movements during procedure, postoperative pain and fatigue levels, recovery time, injection pain, dizziness, headache, nausea and vomiting, satisfaction of endoscopists and patients, as well as postoperative sleep quality and appetite. The primary hypothesis is that lidocaine, when used as an adjunct to propofol sedation, will reduce the incidence of intraoperative desaturation and hypotension in elderly patients undergoing same-visit bidirectional endoscopy. This trial will be conducted and reported in accordance with the Consolidated Standards of Reporting Trials guidelines.

As a preferred sedative for gastrointestinal endoscopy, propofol offers advantages over conventional agents like benzodiazepines, including faster induction, quicker recovery, and enhanced patient satisfaction [23]. However, its administration is associated with a relatively high risk of cardiorespiratory adverse events. Reported complication rates vary considerably, ranging from 20% to 60%, depending on the procedure type and the sedation strategy employed [8,11,22,24]. In elderly patients, common age-related physiological changes, such as reduced hepatic and renal drug clearance, heightened sensitivity to sedative agents, impaired protective airway reflex and increased secretions production during procedures, further increase the risk of sedation related complications [2,25]. According to the 2006 guidelines on sedation for gastrointestinal endoscopy, over-sedation remains a major contributor to adverse events, and reduced sedative dosages are recommended in older populations [26].

Lidocaine is a cost-effective, commonly used local anesthetic with well-established antinociceptive and anti-inflammatory properties [27]. Intravenous lidocaine administration has been shown to reduce intraoperative volatile anesthetics by approximately 30–40%, as well as decrease propofol requirements during total intravenous anesthesia [28,29]. During endoscopic procedures, patient discomfort primarily arises from visceral nociception induced by distension and traction of the gastrointestinal tract. The sedative-sparing effect of intravenous lidocaine has also been demonstrated in endoscopic settings. In a randomized, placebo-controlled trial involving 40 patients undergoing colonoscopy, adjunctive intravenous lidocaine infusion reduced propofol consumption by 50% (mean dose: 58 mg vs 121 mg) and significantly improved postoperative pain and fatigue levels [11]. In addition to the propofol-sparing effect, lidocaine infusion has been shown to enhance the ventilatory response to carbon dioxide in humans [30]. Furthermore, Intravenous lidocaine at doses of 1–2 mg/kg is effective in preventing laryngospasm during general anesthesia [31]. Collectively, these effects may contribute to a reduction in the incidence of sedation-related adverse events. Several patient- and disease-related factors, including age, BMI, history of hypertension, COPD, and diabetes mellitus, are considered as potential confounders for sedation-related adverse events [32]. These variables will be adjusted for using multivariate logistic regression or generalized linear models to minimize bias and more precisely estimate the independent effect of the intervention on the study outcomes.

In elderly individuals, a significant increase in the apparent volume of distribution of lidocaine has been observed. They also exhibit a markedly prolonged elimination half-life compared with younger adults (2.7 vs. 1.6 h) [33]. Although hepatic blood flow is reduced in the elderly, previous studies have shown no significant change in the plasma metabolic clearance of lidocaine in this population [34]. Consequently, the recommended initial loading dose is the same as that for younger adults, whereas the maintenance infusion should be reduced to mitigate the risk of drug accumulation [33]. In the general population, the pharmacological effects of a single intravenous bolus of lidocaine typically persist for 10–20 min [27]. In our previous study involving patients undergoing same-visit bidirectional endoscopy, the median procedure time was 18–20 min [7]. Therefore, in the present protocol, we adopted a loading dose of 1.5 mg/kg, consistent with the regimen described by Forster et al. [11], without the use of continuous infusion. To our knowledge, this will be the first multicenter randomized controlled trial to evaluate whether adjunctive lidocaine administration can reduce the incidence of cardiorespiratory complications associated with propofol-based sedation in elderly patients undergoing same-visit bidirectional endoscopy.

This study has several limitations. First, intravenous lidocaine may elicit a metallic taste, potentially introducing subtle unblinding cues. Second, adjunctive lidocaine is administered prior to propofol to explore a potentially more suitable sedation strategy for elderly patients, however, this sequence may also introduce the risk of unblinding. To mitigate this, a low dose of sufentanil is administered before lidocaine or placebo, and intravenous access is established *via* the antecubital vein in our study to minimize sensory cue. Third, patients older than 80 years are excluded from this study, as we believe that the optimal sedation regimen for the very elderly patients should be determined based on the findings of the current study.

In conclusion, this multicenter randomized controlled trial will assess the impact of intravenous lidocaine as an adjuvant to propofol-based sedation on the incidence of desaturation and hypotension in elderly patients undergoing same-visit bidirectional endoscopy. Regardless of the outcome, the findings of this study will provide valuable evidence to guide and optimize sedation practices in this vulnerable population.

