## Introduction

The incidence of gastrointestinal diseases increases with advancing age, and endoscopic procedures are frequently performed in elderly patients for both diagnosis and therapeutic purposes [1–3]. To improve procedural efficiency and quality of care, an increasing number of elderly individuals opt to undergo esophagogastroduodenoscopy and colonoscopy during the same hospital visit [4]. Sedation is commonly employed during these procedures to enhance patient comfort and procedural satisfaction [5]. However, age-related physiological changes such as reduced drug metabolism and increased sensitivity to sedative agents heighten the risk of sedation-related complications in elderly patients [3]. Accordingly, minimizing sedative exposure is essential for enhancing the safety profile of gastrointestinal endoscopy in this population.

Propofol remains the most widely used agent for intravenous anesthesia in clinical practice due to its rapid onset, short duration of action, and favorable recovery profile [6,7]. Nevertheless, it is associated with dose-dependent adverse effects, most notably hypotension and respiratory depression [8,9]. These complications are particularly concerning in elderly patients and may adversely affect both intraoperative stability and postoperative recovery [9,10]. Intravenous lidocaine has emerged as a promising adjunct to sedation protocols. Prior studies have demonstrated that intravenous lidocaine reduces propofol requirements and alleviates post-colonoscopy visceral pain [11]. Moreover, recent evidence suggests that intravenous lidocaine may significantly improve sedation quality and endoscopist satisfaction, and even reduce the incidence of sedation-related adverse events during endoscopic retrograde cholangiopancreatography (ERCP) procedures [12–14]. It remains uncertain whether the adjunctive use of lidocaine during same-visit bidirectional endoscopy can reduce the incidence of sedation-related adverse events in elderly patients.

This multicenter, randomized, double-blind, placebo-controlled trial is designed to test the hypothesis that lidocaine, administered as an adjunct to propofol sedation, lowers the incidence of desaturation and hypotension during same-visit bidirectional endoscopy in elderly patients.

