### Eligibility criteria

Eligible participants were (1) aged between 65 and 80 years, (2) American Society of Anesthesiologists (ASA) physical status classification of I to Ш, (3) body mass index (BMI) between 18 and 30 kg/m^2^, (4) scheduled to undergo same-visit bidirectional endoscopy under sedation.

Exclusion criteria were as follows: (1) contraindications to endoscopic procedures or refusal of anesthesia, (2) uncontrolled or potentially life-threatening cardiovascular and respiratory conditions, including acute coronary syndrome, severe uncontrolled hypertension (systolic blood pressure ≥ 180 mmHg or diastolic blood pressure ≥ 110 mmHg), serious arrhythmias, heart failure, acute respiratory infections, asthma exacerbations, active hemoptysis, severe hepatic dysfunction (Child-Pugh class C or higher), acute upper gastrointestinal bleeding with shock, severe anemia (hemoglobin < 6 g/dL), or gastrointestinal obstruction with gastric content retention, (3) absence of an accompanying escort or guardian, (4) known allergies to sedatives or anesthetics, or a significant personal or family history of allergic reactions.

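### Age is the only adjustment covariate without a listed treatment interaction, BMI is dichotomised for its interaction, and the remark on patients over 80 goes further than data from ages 65 to 80 can

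*Protocol article*

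**What the plan says.** Under Eligibility criteria, participants are "aged between 65 and 80 years". The limitations paragraph of the Discussion confirms that "patients older than 80 years are excluded from this study" and gives as the reason the authors' belief that "the optimal sedation regimen for the very elderly patients should be determined based on the findings of the current study".

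Under Statistical analysis, the outcome models are fitted "adjusting for relevant baseline covariates (age, BMI, history of hypertension, chronic obstructive pulmonary disease [COPD], and diabetes mellitus) and study center". The subgroup analyses of the primary outcome are for "predefined subgroups, including BMI (< 25 kg/m^2^ vs ≥ 25 kg/m^2^), history of hypertension (yes vs no") and "history of COPD (yes vs no), history of diabetes mellitus (yes vs no), and study center (leading center vs participating center"), with interactions tested by logistic regression. Age is not on that list.

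The Introduction rests the trial on age: "age-related physiological changes such as reduced drug metabolism and increased sensitivity to sedative agents heighten the risk of sedation-related complications in elderly patients". The Discussion repeats the argument and names age first among the factors thought to confound sedation-related events. Age and BMI are both recorded under Data collection, and BMI is restricted to 18 to 30 kg/m² at entry.

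**The concern.** The adjustment list and the interaction list match item by item except for age. Age as a main effect in the adjusted model describes how the risk of desaturation or hypotension varies with age. It does not show whether the lidocaine effect varies with age. For a trial justified by age-related vulnerability, that is a natural exploratory question, and on the published list it is the one left out.

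The BMI interaction is tested by cutting a continuous measurement at 25, which discards information in a test that already has little power.

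The third matter is interpretation. The sentence on the very elderly names no further study and ties their regimen to findings from patients aged 65 to 80. If a reader takes it literally, a result could be carried to a group that contributes no data, on an assumption of constant effect that no listed analysis examines.

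**Working it through.** **1. The two lists side by side (Statistical analysis).**

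| Covariate | Adjusted for | Listed interaction |
|---|---|---|
| Age | yes | no |
| BMI | yes | yes, cut at 25 |
| Hypertension | yes | yes |
| COPD | yes | yes |
| Diabetes | yes | yes |
| Study center | yes | yes, leading vs participating |

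The difference between the lists is age alone.

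**2. The plan's own figure.** Inputs from Sample size calculation: a reduction of 10 points to 20%, so a control risk of 30%; two-sided α 0.05; power 80%. With unpooled variance, n = (0.30 × 0.70 + 0.20 × 0.80) × (1.960 + 0.842)² / 0.10² = 290.4 per group, which matches the stated 290. Allowing for 10% dropout, 290/0.9 rounds up to 323 and 291/0.9 to 324. The sample size is not in question, and 290 per arm is used below.

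**3. How precisely the effect is known at a given age.** The SE of the overall log odds ratio is √[1/(290 × 0.30 × 0.70) + 1/(290 × 0.20 × 0.80)] = 0.195. With a linear treatment-by-age term, the SE at age a is approximately 0.195 × √[1 + (a − mean)²/SD²]. The document gives no age distribution. Assume first that ages are uniform over 65 to 80: mean 72.5, SD = 15/√12 = 4.33.

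- At 72.5: SE 0.195; exp(1.96 × 0.195) = a factor of 1.5 either side.
- At 80: 0.195 × √(1 + 7.5²/4.33²) = 0.39; a factor of 2.1.
- At 85: 0.195 × √(1 + 12.5²/4.33²) = 0.60; a factor of 3.2.

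A simulation of 1,500 trials under the same assumptions gave mean SEs of 0.198, 0.384 and 0.593.

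Two other assumed age distributions show the range at 85:

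- Half the patients at 65 and half at 80, the widest spread the entry range allows (SD 7.5): 0.195 × √(1 + 12.5²/7.5²) = 0.38; a factor of 2.1.
- A density falling linearly from 65 to zero at 80 (mean 70, SD = 15/√18 = 3.54): 0.195 × √(1 + 15²/3.54²) = 0.85; a factor of 5.3.

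All of these also assume that a straight line fitted over 65 to 80 continues to 85, which no data in the trial can test.

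**4. What an age interaction could detect within 65 to 80.** Take a deliberately strong trend (assumed): OR 0.33 at 65 rising to 1.0 at 80, ages uniform.

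- Continuous age: slope = 1.109/15 = 0.0739 per year; SE = 0.195/4.33 = 0.0450; z = 1.64; power = Φ(1.64 − 1.96) = 38%. Simulation: 38%.
- Split at 72.5: difference between halves = 1.109/2 = 0.554; SE = 2 × 0.195 = 0.390; z = 1.42; power = Φ(1.42 − 1.96) = 30%. Simulation: 29%.

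The continuous test is better, but neither is well powered. In a two-level version with 30% vs 20% in the younger stratum and no effect in the older, power is about 22%, 27% and 30% if the older stratum holds 20%, 30% and 50% of patients (assumed shares).

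**5. BMI.** The same reasoning applies. If the effect changes roughly linearly with BMI, a cut throws away power, as the split does for age. The document gives no BMI distribution, so the loss is not quantified here.

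**The case against.** The best defence of the Discussion sentence is that it is a disclosed limitation and can be read as staged research: study 65 to 80 first, then let the findings inform work in older patients. No objective, hypothesis, outcome, analysis or conclusion elsewhere in the article makes a claim about patients over 80. This stands as a reading of intent. It does not make the wording clear, since no later study is mentioned.

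On the interaction list, no rule requires every adjustment covariate to be a subgroup. The list opens with *including*, and Data collection refers to a prespecified analysis plan that is not shown. Age may therefore be covered there, and it cannot be said that the question has been left to post hoc choice. The point is limited to what the article lists.

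A further objection is that an age interaction has low power. That is true, but the calculation in step 4 for a two-level stratum gives the same power for any binary factor on the list with those shares, and these analyses are exploratory in any case. A cut at 25 for BMI is conventional and prespecified. It is less efficient than a continuous test, not an error.

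A reader might also infer from the half-life figures in the Discussion (2.7 vs 1.6 h) that the lidocaine effect changes with age inside the trial. The document does not support this. Those figures compare elderly with younger adults, the text goes on to report unchanged plasma clearance and the same recommended loading dose, and accumulation is raised only for maintenance infusion, which this trial does not use. The Introduction's statement that age raises complication risk supports age as a covariate. It is not evidence of a changing treatment effect.

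**Conclusion.** A minor point, in two separate parts that should not be run together.

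First, the published interaction list omits age, the one adjustment covariate not covered, and handles BMI less efficiently than the collected data allow. Both are inexpensive improvements to exploratory analyses.

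Second, the sentence on patients over 80 is worded more strongly than the trial can bear. It is tempting to conclude that the missing age interaction is what prevents use of the result above 80. The figures say otherwise: with that interaction included, the limits on the odds ratio at 85 would still be about a factor of 3.2 either side under uniform ages, and between about 2.1 and 5.3 over the other age distributions tried, all under linearity. The overall result remains indirect evidence for older patients, but it cannot determine their regimen.

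The figures rest on 290 evaluable patients per arm, the planned 30% and 20% risks and the assumed age distributions. The detection figures also rest on the assumed trend and strata. The comparison of the two lists and the wording point need none of these. The primary test and sample size are unaffected.

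**What to change.** 1. In Statistical analysis, add treatment by continuous age to the prespecified exploratory interactions, and report it as the estimated effect with its confidence band across 65 to 80.
2. Test the BMI interaction on the continuous scale and keep the cut at 25 for display only.
3. In the Discussion, limit conclusions to ages 65 to 80 and say that patients over 80 need their own data. If staged research is what was meant, say so. Do not cite the pharmacokinetic figures as evidence that the effect changes within 65 to 80.

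The cost is one added model term, one changed term and one reworded sentence. Age and BMI are already collected, and the change can be made before the database is locked. The downside is one more low-power exploratory test, which should be labelled as such, with a non-significant interaction not taken as proof of a constant effect.
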